#### Study design

The study includes two stages. In stage I, the study observes the incidence of feeding intolerance, parenteral nutrition conditions, spontaneous fecal discharge conditions, growth and development conditions and the incidence of other preterm children’s complications in the preterm children in the two groups during the NICU stay. In this stage, different feeding methods and parenteral nutrition are regulated according to the gestational age, birth weight and days after birth of the preterm children, and unified diagnostic criteria and treatment methods for different complications are developed. In stage II, the study follows up the growth and development conditions of the preterm children in the two groups on a regular basis after discharge from the NICU.

#### Introduction to the formulae

The two kinds of formula for feeding during the NICU stay and the formula for feeding after discharge from the NICU are all Dumex, a brand of French Danone-Nutricia for early life nutrition. In this study, the gestational age of all preterm children when discharged from the NICU is all ≥34 weeks, and thus formula suitable for 0 to 6-month-old infants is uniformly chosen for them after discharge. The ingredients of such formulae are shown in Table 1.

**Table 1 Tab1:** Table of ingredients of the three formulae

Ingredients	Preterm children’s formula (/100 ml)	Extensively hydrolyzed formula (/100 ml)	Formula for 0 to 6-month-old infants (/100 ml)
Energy (kcal/KJ)	80/336	66/278	67/282
Osmolality (mOsmol/L)	360	250	-
Fat (g)	3.8	3.5	3.5
α-linolenic acid (mg)	44	58	42
Linoleic acid (g)	0.6	0.41	0.42
Oleic acid (g)	1.3	1.2	-
Medium-chain triglyceride content (%)	30 %	40 %	-
Protein (g)	2.6 (60 % whey protein and 40 % casein)	1.6 (100 % whey protein)	1.4
Carbohydrates	8.4	6.9	7.1
Lactose (g)	5.6	2.8	-
Prebiotics (galactooligosaccharides, polyfructose) (g)	0.8	0.8	0.8
Arachidonic acid (mg)	19	6.6	12
Docosahexaenoic acid (mg)	15	6.6	12
Taurine (mg)	5.5	5.3	5.4
L-carnitine (mg)	1.8	1	1.5
Nucleotides (mg)	3.4	3.2	3.0
Vitamin A (μg)	359	52	65
Vitamin D (μg)	3	1.3	0.95
Vitamin E (mg)	3.5	1	1.2
Vitamin K1 (μg)	6	4.7	5.4
Vitamin B1 (μg)	139	50	58
Vitamin B2 (μg)	199	99	103
Vitamin B6 (μg)	119	40	48
Vitamin B12 (μg)	0.24	0.18	0.31
Nicotinamide acid (μg)	2352	432	517
Folic acid (μg)	35	9	11
Pantothenic acid (μg)	876	327	354
Vitamin C (mg)	17	9	9.2
Biotin (μg)	3.5	2.2	2.3
Choline (mg)	17	10	16
Inositol (mg)	24	3.2	3.8
Sodium (mg)	70	20	20
Potassium (mg)	80	75	69
Copper (μg)	80	40	48
Magnesium (mg)	8	5.1	5.7
Iron (mg)	1.6	0.53	0.71
Zinc (mg)	1.1	0.5	0.5
Manganese (μg)	10	7.4	7.5
Calcium (mg)	100	47	52
Phosphorus (mg)	56	26	31
Iodine (μg)	25	12	11
Chlorine (mg)	85	41	48
Selenium (μg)	4.5	1.5	2.2

### Stage I: NICU stay

Feeding timePreterm children without obvious high-risk factors are fed within 24 hours after birth.The feeding of preterm children with birth weight <1000 g, obvious history of asphyxia at birth (Apgar score ≤5), severe infection (sepsis, purulent meningitis, etc.), severe pneumonia or neonatal respiratory distress syndrome (NRDS) requiring intubation and mechanical ventilation should be postponed to 24–72 h after birth according to the situation.During the period when full enteral nutrition is not achieved, partial parenteral nutrition is given according to the daily amount of fluid and energy required by the children; when the children experience feeding intolerance and necrotizing enterocolitis and need to be fasting, complete parenteral nutrition is given; after the conditions are stable, the children gradually switch to enteral nutrition and are fed until discharge or transfer into DRI.Children in the two groups are fed with ordinary formula after discharge or transfer to DRI.Feeding methodsFor preterm children with a gestational age of <32 weeks, since their sucking-swallowing action is uncoordinated and respiratory function is not maturely developed, the children are given tube feeding (nasogastric tube or orogastric tube) using the intermittent infusion feeding method. Every time before feeding, the stomach contents are drawn to learn about gastric residual volume (GRV) and nature.Children suspected of suffering from gastroesophageal reflux or delayed gastric emptying are fed by adopting intermittent/continuous infusion feeding method with an infusion pump.Preterm children with a gestational age of 32–34 weeks are given direct bottle feeding.Children with weak sucking ability yet normal gastric emptying are given bottle feeding first, and then the remaining milk is given by tube feeding.Children with nasal continuous positive airway pressure (nCPAP) or intubation and mechanical ventilation are given tube feeding;During tube feeding or fasting period, the children are given non-nutritive sucking (NNS).Feeding milk volumeInitial feeding milk volume: according to birth weight, the children are fed from different initial milk volume once every two hours, as shown in Table 2.The milk volume begins to increase in the absence of feeding intolerance in 24-h observation, and the rates for milk increasing are shown in Table 2.

**Table 2 Tab2:** Initial feeding milk volume and increasing rate in the two groups of preterm children

Birth weight (g)	Initial feeding milk volume (ml/kg)	Increasing rate (ml/kg/d)
<1000	1.0	12
1000–1500	1.0–2.0	12–24
1501–2000	2.0	24–36
>2000	2.0	36Fluid amount control [14, 47]

Fluid amount includes the total amount of enteral nutrition, parenteral nutrition and all other intravenous and oral medications. If birth weight is <1500 g, the fluid amount in the first 24 hours after birth is 80–100 ml/(kg/d); if birth weight is ≥1500 g, the fluid amount in the first 24 hours after birth is 60–100 ml/(kg/d); then the amount is incremented at a rate of 15–20 ml/(kg/d) to reach 150 ml/(kg/d) by the end of the first week; daily fluid amount is increased or decreased by 10–20 ml/kg on the basis of the fluid amount that day according to different clinical conditions (light therapy, incubator, ventilator, heart and lung function, urine amount, systemic edema conditions, biochemical monitoring indicators, etc.), usually no more than 180 ml/(kg/d).5.Calorie control [14, 47]

Calorie includes the total calories provided by enteral feeding and parenteral nutrition. The calorie on the first day is 40 kcal/kg and then incremented at a rate of 10 kcal/(kg/d). Parenteral nutrition is stopped when enteral nutrition reaches 80–100 kcal/(kg/d), and enteral nutrition 100–120 kcal/(kg/d) is the criterion to achieve full enteral nutrition.6.Parenteral nutrition (PN) [14, 47]Vessel selection: peripheral vein or central vein, central vein includes peripherally inserted central catheter (PICC) and umbilical venous catheter (PVC).Method: all children adopt “all in one” parenteral nutrition. The nutrient solution used for daily parenteral nutrition is uniformly prepared inside on a clean bench at the hospital’s Intravenous Nutrition Preparation Center according to the doctor’s instructions that day, and attention should be paid to the sequence of mixing during preparation. After preparation the solution is evenly infused via the infusion pump within 24 hours. The total amount of parenteral nutrition fluid and compounding ratio of all nutrients are calculated according to the child’s total fluid amount required that day, total calorie, milk intake the day before and possible total milk intake that day.Children’s compound amino acid (6 %) 1.0–1.5 g/(kg/d) is added within 24 hours after birth, which is later incremented up to 3.5–4.0 g/(kg/d) at a rate of 0.5 g/(kg/d); medium and long-chain fat emulsion 0.5 g/(kg/d) is added within 24 hours after birth, which is later incremented up to 3.0 g/(kg/d) at a rate of 0.5 g/(kg/d).Carbohydrates ≤15 g/(kg/d), providing 40–50 % of the total energy; amino acids ≤3.5–4.0 g/(kg/d), providing 15–20 % of the total energy, fat emulsion ≤3.0 g/(kg/d), providing 40–50 % of the total energy.Sodium ions 2.0–3.0 mmol/L and potassium ions 1.0–2.0 mmol/L are supplemented daily, but within 3 days after birth, no potassium is supplemented in principle unless the child is suffering from hypokalemia.A variety of water-soluble and fat-soluble vitamins 0.5–1.0 ml/(kg/d) are supplemented.If the child has cholestasis, the amount of intravenous fat emulsion is reduced.The concentration and rate of intravenous nutritive sugar are adjusted according to the child’s blood glucose monitoring. In case of PVC or PICC, the sugar concentration is ≤15 %; when peripheral intravenous infusion is adopted, the sugar concentration is ≤12.5 %. The child’s blood glucose is controlled at 3.0–7.0 mmol/L.7.Diagnostic criteria for and treatment of various complications:Diagnostic criteria for and clinical treatment of feeding intolerance [48, 49]

Children in line with any of the following six criteria can be diagnosed with feeding intolerance:Gastric residual liquid >50 % of the amount of previous feedingVomiting ≥3 times/day, or the vomitus is bile-likeGastric residual liquid or vomitus is bile-like or coffee grounds-likeAbdominal distension (abdominal girth is increased by ≥1.5 cm within 24 hours, with intestinal type), and abdominal distension caused by the use of nCPAP should be ruled outRequired fasting >2 mealsBlood in the stool or fecal occult blood positive, but it is required to rule out NEC based on the general conditions, blood indicators and abdominal X-ray examination of children

Clinical treatments:Amount of gastric residue: for children with tube feeding, draw the residual milk in the stomach every time before feeding.If birth weight is <1500 g, and gastric residue is <2 ml or if birth weight is ≥1500 g and gastric residue is <3 ml or gastric residue is <30 % of the amount of previous feeding, continue feeding and closely observe.If gastric residue is 30–50 % of the amount of previous feed, reduce the amount of feeding.If gastric residue is >50 % of the amount of previous feeding, fast for one meal, and continue feeding by the original feeding plan after the condition is improved.If there is bile-like or coffee grounds-like liquid in the gastric residual liquid or vomitus, stop feeding.Abdominal distension: measure the abdominal girth at fixed parts every time before feeding. If the abdominal girth is increased by ≥1.5 cm, reduce the amount of feeding or fast for one meal, and continue feeding by the original feeding plan after the abdominal distension condition is improved.If daily vomiting occurs >3 times, do not increase the milk volume or reduce the amount of feeding.In the event of blood in the stool or fecal occult blood positive, stop feeding.2.Diagnostic and treatment reference criteria for necrotizing enterocolitis (NEC) [50] are shown in Table 3.

**Table 3 Tab3:** Modified Bell staging criteria for neonatal necrotising enterocolitis

Staging	Systemic symptoms	Gastrointestinal symptoms	Radiological signs	Treatment
IA Suspected NEC	Temperature instability, apnoea, bradycardia, lethargy	Gastric retention, mild abdominal distension, fecal occult blood positive	Normal or intestinal dilation, mild ileus	Absolute fasting, gastric decompression, antibiotic therapy for 3 days, waiting for pathogen culture results
IB Suspected NEC	Same as IA	Bright-red blood from rectum	Same as IA	Same as IA
IIA proven NEC (mildly ill)	Same as IA	Same as IA or IB, plus absent bowel sounds, and (or) abdominal tenderness,	Intestinal dilation, ileus, pneumatosis intestinalis	Same as IA, absolute fasting. If 24–48 h culture shows no abnormality, use antibiotics for 7– 10 days
IIB proven NEC (moderately ill)	Same as IIA, plus mild metabolic acidosis and mild thrombocytopenia	Same as IIA,plus absent bowel sounds, definite abdominal tenderness, and (or) abdominal cellulitis or right lower quadrant mass	Same as IIA, plus portal vein gas, and (or) ascites	Same as IIA, absolute fasting. Supplement blood volume, treat acidosis, and use antibiotics for 14 days
IIIA Advanced NEC (severely ill, bower intact)	Same as IIB, plus hypotension, bradycardia, severe apnea, mixed acidosis, DIC, neutropenia, anuria	Same as IIB, plus signs of generalized peritonitis, abdominal distension or marked tenderness, and redness and swelling of abdominal wall	Same as IIB, ascites	Transfer to the Surgical Department of Children’s Hospital for observation
IIIB Advanced NEC (severely ill, bowel perforated)	Same as IIIA, plus suddenly aggravation of conditions	Same as IIIA, plus sudden aggravation of abdominal distension	Same as IIB, pneumoperitoneum	Transfer to the Surgical Department of Children’s Hospital for surgery

*NEC* necrotising enterocolitis, *DIC* disseminated intravascular coagulation3.Diagnostic criteria for and clinical treatment of cholestasis:Diagnostic criteria [51]: in line with any of the first two criteria:Total bilirubin (TB) <5 mg/dl and direct bilirubin (DB) >1.0 mg/dlTB >5 mg/dl and DB >20 % of TBElevated total bile acid (TBA) levels alone cannot serve as a diagnostic criterion for cholestasis4.Diagnosis and clinical treatment of parenteral nutrition-associated cholestasis (PNAC):

Diagnostic criteria for PNAC [52]:Continuous parenteral nutrition ≥14 daysSerum DB >34umol/L (2 mg/d1)Clinical manifestations of yellowish discoloration of skin, hepatosplenomegaly, elevated transaminase levels and (or) lighter stool colorExclusion of other diseases causing cholestasis (various biliary malformations causing biliary obstruction, hereditary metabolic diseases and hepatitis caused by bacterial and viral infections)

Clinical treatment of PNAC:Protect the liver and gallbladder: ursodesoxycholic acid 15 mg/(kg/d), three times daily, by mouthDo not lightly fast; increase enteral nutrition, reduce the proportion of parenteral nutrition, and medium and long-chain fat emulsion ≤1 g/(kg/d)Additionally supplement vitamin E 10 mg/(kg/d), twice daily, by mouth5.Diagnostic criteria for and clinical treatment of congenital hypothyroidism [53].

Diagnostic criteria: 1 week after birth, draw blood to test serum thyroid-stimulating hormone (TSH), total triiodothyronine (TT_3_), total thyroxine (TT_4_), free triiodothyronine (FT_3_) and free thyroxine (FT_4_). If blood test shows no abnormality but there are clinically suspicious symptoms of hypothyroidism, retest the thyroid function. Suspicious symptoms of preterm children’s hypothyroidism include persistent jaundice, lethargy, less crying, low and weak crying, slow heart rate, low and blunt heart sounds, poor digestion (weak sucking, feeding intolerance), recurrent hypoglycemia, etc.If blood TSH is >10 mU/L and FT_4_ is decreased, the child will be diagnosed with congenital hypothyroidism.If blood TSH is >10 mU/L and FT_4_ is normal, the child will be diagnosed with high TSH hyperlipidemia.If blood TSH is normal or decreased and FT_4_ is decreased, the child will be diagnosed with secondary or central hypothyroidism.

Clinical treatment:In line with criterion (1), levothyroxine (Euthyrox) from a starting therapeutic dose of 10–15ug/(kg/d), daily, by mouth.In line with criterion (2), retest 1 week later. If TSH is still >10 mU/L, give Euthyrox 4–8ug/kg/d, daily, by mouth.In line with criterion (3), retest 1 week later. If FT_4_ is still decreased, give Euthyrox 4– 8ug/kg/d, daily, by mouth.If TSH always maintains at 6–10 mU/L, without treatment, regularly follow up thyroid function.If FT_4_ and TSH are normal, children with decreased TT_3_ or TT_4_ are given no treatment.For children with abnormal test results, draw blood for retest in 1–2 weeks. Adjust the therapeutic dose based on the concentrations of blood TSH and FT_4_ and the children’s weight.6.Diagnostic criteria for and clinical treatment of hypocalcemia [54]

Diagnostic criteria:

Total serum calcium is less than 1.75 mmol/L (7.0 mg/dl) or free calcium is less than 0.9mmom/L (3.5 mg/dl).

Clinical treatment:For children with clinical seizures or heart rhythm disorders, which cannot be explained by other diseases, give them slow intravenous injection of 10 % calcium gluconate 2 ml/kg, and use 5 % glucose injection after dilution by onefold. Then according to the retest result, decide whether to continue intravenous injection or switch to oral medication.For children with stable conditions, give them tube feeding or oral 10 % calcium gluconate.

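### In larger infants fed from day 1, the Table 2 feed advance and the total-calorie schedule contradict each other, so time to full enteral nutrition and PN time depend on which rule staff follow

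*Protocol article*

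**What the plan says.** All of this is in the protocol article under Stage I: NICU stay, unless noted.

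- **Feeds.** Infants are "fed from different initial milk volume once every two hours". Table 2 starts every infant above 1500 g at 2.0 ml/kg. The next-to-top row reads "1501–2000 2.0 24–36"; above 2000 g the advance is 36 ml/kg/d, with no range. The condition for advancing is tolerance: "The milk volume begins to increase in the absence of feeding intolerance in 24-h observation".
- **Start of feeding.** Infants without obvious high-risk factors start within 24 hours of birth. For high-risk infants, feeding "should be postponed to 24–72 h after birth according to the situation".
- **Calories.** "Calorie includes the total calories provided by enteral feeding and parenteral nutrition". The schedule is: "The calorie on the first day is 40 kcal/kg and then incremented at a rate of 10 kcal/(kg/d".
- **PN stop and full feeding.** Both are defined by enteral calories: PN stops at 80–100 kcal/kg/d, and full enteral nutrition is 100–120 kcal/kg/d.
- **Fluid.** "Fluid amount includes the total amount of enteral nutrition, parenteral nutrition and all other intravenous and oral medications". From a birth weight of 1500 g it starts at 60–100 ml/kg/d and rises by 15–20 ml/kg/d "to reach 150 ml/(kg/d) by the end of the first week". Daily adjustments of 10–20 ml/kg are allowed, usually up to 180 ml/kg/d.
- **Energy density** (Table 1): preterm formula (control) 80 kcal per 100 ml, EHF 66 kcal per 100 ml.
- **Endpoints and blinding.** Time to full enteral nutrition and time of parenteral nutrition are secondary endpoints (Outcomes). Physicians and nurses can tell the formulae apart (Randomization and blinding).

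**The concern.** Table 2 prescribes a volume of milk, and the calorie paragraph prescribes a total energy intake that includes this milk. If the milk alone carries more energy than the scheduled total, one of the two is not being followed, and no sentence ranks them.

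This matters statistically because the two affected endpoints are meant to be read as consequences of tolerance. Where the rules collide, they partly record which paragraph the ward obeyed. The collision also differs by arm: at equal volume the denser control formula overshoots the calorie schedule sooner and by more. A choice of rule, made by staff who know the formula, can therefore create or remove a between-arm difference in an infant who tolerates feeds perfectly.

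**Working it through.** **Check of the plan's own figure.** Lowest fluid path from 1500 g: 60 + 15 × 6 = 150 ml/kg/d on day 7, as stated.

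**Formulas** (feeding from day 1, no interruption):
- Milk volume on day d = 12 × 2.0 + rate × (d − 1) = 24 + rate × (d − 1) ml/kg.
- Milk energy = volume × 0.80 (control) or × 0.66 (EHF) kcal/kg.
- Scheduled total = 40 + 10 × (d − 1) kcal/kg.

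**Advance of 36 ml/kg/d** (all above 2000 g; upper end of 1501–2000 g):

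| Day | Milk ml/kg | Control kcal/kg | EHF kcal/kg | Scheduled total kcal/kg |
|---|---|---|---|---|
| 1 | 24 | 19.2 | 15.8 | 40 |
| 2 | 60 | 48.0 | 39.6 | 50 |
| 3 | 96 | 76.8 | 63.4 | 60 |
| 4 | 132 | 105.6 | 87.1 | 70 |
| 5 | 168 | 134.4 | 110.9 | 80 |

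Milk alone exceeds the total from day 3 in both arms. On day 4 the excess is 105.6/70 − 1 = 51 % (control) and 87.1/70 − 1 = 24 % (EHF).

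**Advance of 24 ml/kg/d** (low end of 1501–2000 g):
- Control on day 4: 96 × 0.80 = 76.8 against 70, so exceeded.
- EHF on day 5: 120 × 0.66 = 79.2 against 80, not exceeded. On day 6: 144 × 0.66 = 95.0 against 90, slightly exceeded.

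**Day on which enteral intake reaches 100 kcal/kg** (lower limit of the full-feeding criterion). The schedule itself reaches 100 on day 7 (40 + 60), and 80 on day 5.

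| Advance | Rule followed | Control | EHF | Difference |
|---|---|---|---|---|
| +36 | Table 2 | 4 | 5 | 1 day |
| +36 | Calorie figure as upper target | 7 | 7 | 0 |
| +24 | Table 2 | 6 | 7 | 1 day |
| +24 | Calorie figure as upper target | 7 | 7 | 0 |

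For EHF at +24, neither 80 nor 100 kcal/kg is delayed by the calorie schedule.

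**PN time.** At +36 on day 3, enteral intake (76.8 and 63.4) is below 80, so PN continues by the stopping rule. The scheduled total leaves 60 − 76.8 = −16.8 kcal/kg (control) and 60 − 63.4 = −3.4 kcal/kg (EHF) for it. At +24, control on day 4 has 70 − 76.8 = −6.8. With the calorie figure as upper target, 80 kcal/kg at +36 moves from day 4 to day 5 in both arms.

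**Sensitivity to the start of feeding, +36:**
- One day later: the schedule is still exceeded, by control on day 4 (76.8 against 70) and by EHF on day 5 (87.1 against 80). Full feeding is day 5 (control) and day 6 (EHF) by Table 2, against day 7.
- Two days later: control moves from day 6 to day 7; EHF is day 7 either way.
- Three days later: no shift in either arm.

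**Sensitivity to the starting volume.** Reading 2.0 ml/kg as a daily volume, +36 still exceeds the schedule on day 4: 110 × 0.80 = 88.0 and 110 × 0.66 = 72.6 against 70.

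**Fluid.** At +36, milk passes the lowest path on day 3 (96 against 90). On the highest path (100 + 20 per day) it fits on day 3 (96 against 140) and on day 4 (132 against 150). On day 5, 168 passes 150 but not the usual limit of 180, and by then both arms are above 100 kcal/kg enteral.

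**The case against.** The strongest reply is that milk is an input and PN the remainder. The PN paragraph computes each day's PN from total fluid, total calories and milk intake. The only stated condition for advancing milk is absence of intolerance, and the stated reasons to reduce or stop it are intolerance signs or NEC. Nothing tells staff to hold milk for a calorie figure, and the same section writes ≤ where it means a cap. On this reading milk follows Table 2 and PN shrinks to nothing.

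Much of this stands. A reader might infer that the calorie schedule forbids full feeding before day 7; the text states no ceiling, so that result is conditional on reading the figure as an upper target. But the reply does not dispose of the point. Milk first, PN as remainder, is a plausible inference and not a stated precedence. The calorie figure is given as an exact total that includes milk, without an at-least. And even on this reading PN is to continue below 80 kcal/kg enteral on days when the scheduled total has no room for it.

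A second reply is that few infants meet the conditions: high-risk infants start late, and the sample-size section expects 75–85 % with intolerance. Interruptions do reduce the conflict. The same figures leave 15–25 % with no intolerance event, and after some episodes feeding resumes on the original plan after one missed meal. The documents give no birth-weight distribution, so the share affected is unknown.

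**Conclusion.** The contradiction between Table 2 and the calorie schedule is established from the protocol's own figures. It is clear at +36 ml/kg/d in both arms, and at +24 ml/kg/d with control formula; with EHF at +24 it is about 5 kcal/kg on day 6 and delays nothing. For an infant advancing without interruption from day 1, the choice of rule moves full enteral nutrition at +36 by 3 days (control) or 2 days (EHF), and at +24 by 1 day (control) or none (EHF). In each case a one-day difference between arms appears or vanishes.

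These shifts assume feeding from day 1, full tolerance, the 100 kcal/kg criterion and, for the later dates, the calorie figure as an upper target. They are shifts for such an infant, not estimates of bias in the trial result, which cannot be quantified from the documents.

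Three wider readings are tempting but unsupported:
- That the fluid schedule is equally incompatible: only its lowest path is passed early, and the text allows adjustment.
- That every infant above 1500 g is affected: the slower advance with EHF and late starts are counter-examples.
- That the primary endpoint is distorted through milk volume: no figure shows this, and the gastric-residual criterion is already a percentage of the previous feed.

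**What to change.** Reconcile Table 2 with the calorie paragraph, and with the lowest fluid path. State whether the calorie figure sizes PN or limits total intake including milk, and give one order of precedence that applies identically in both arms. Which rule should yield is for the clinical team.

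If the reconciled text allows feeds to be held for a reason other than intolerance, enter that reason on the existing daily intake record and show those days by arm when time to full enteral nutrition is reported. Daily milk, PN and total calories are already to be collected, so they can show how the rules were applied in practice.

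The cost is a protocol clarification and, if needed, one extra entry on a form already completed daily. No additional infants are required.

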#### Randomization and blinding

Randomization will be conducted by a researcher not involved in the recruitment and treatment of the participants. Concealed allocation will be performed using a set of random numbers placed in sealed opaque envelopes. The participants who meet the eligibility criteria will be divided into two groups by the physicians on duty via opening the envelopes. Reference to similar study literature is made for randomization [28, 31]. As extensively hydrolyzed milk protein formula and preterm children’s formula are greatly different in color and smell, physicians and nurses can easily distinguish these two formulae. Therefore, the study has chosen single-blinding, which means that only the participants and their guardians are unaware of the milk type.

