### Study design and outcomes

#### Outcomes

The first endpoint variable is the rate of food intolerance in preterm children. The second endpoint variables include (1) time to achieve full enteral nutrition; (2) time of parenteral nutrition; (3) time of NICU stay; (4) meconium drainage time; (5) daily spontaneous fecal discharge conditions; (6) growth and development conditions during the NICU stay and within 3 months after discharge, including daily weight growth rate, weekly body length growth rate and weekly head circumference growth rate; (7) different plasma parameter indicators before discharge from the NICU (total protein (TP), albumin, calcium (Ca), phosphorus (P), and alkaline phosphatase (ALP)). Other endpoint variables include the incidences of neonatal necrotizing enterocolitis, cholestasis, parenteral nutrition-associated cholestasis and congenital hypothyroidism (CH).

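### The protocol gives two non-matching points for ending parenteral nutrition, each a range without a trigger value, so the secondary endpoint of PN time depends on which one unblinded staff apply

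*Protocol article*

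**What the plan says.** Two items under Stage I: NICU stay bear on when PN ends.

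- **Feeding time:** "During the period when full enteral nutrition is not achieved, partial parenteral nutrition is given according to the daily amount of fluid and energy" the child requires. PN is thereby tied to the period before full enteral nutrition.
- **Calorie control:** "Parenteral nutrition is stopped when enteral nutrition reaches 80–100 kcal/(kg/d), and enteral nutrition 100–120 kcal/(kg/d) is the criterion to achieve full enteral nutrition".

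The Outcomes section lists, in order, "1) time to achieve full enteral nutrition; (2) time of parenteral nutrition; (3) time of NICU stay", so time to full enteral nutrition and PN time are separate secondary endpoints. Shortening PN is also part of the secondary objective. The Secondary outcome paragraph of the statistical analysis assigns these times to Kaplan-Meier estimates, logrank tests and Cox models. On blinding, the article states that "physicians and nurses can easily distinguish these two formulae"; only participants and guardians are unaware of the milk type.

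**The concern.** An infant taking, say, 90 kcal/(kg/d) enterally has not met the criterion for full enteral nutrition. The Feeding time item gives that infant PN, while the Calorie control item allows PN to have been stopped. Each limit is also a span of 20 kcal/(kg/d), and the text does not say which value triggers the action.

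This matters because the event that closes the PN interval is a staff decision. Two infants with identical tolerance can be given different PN times according to the rule or value chosen at the bedside. If the choice is unrelated to arm, it adds noise to the comparison. If it were related to arm, it could create or hide part of the shortening that the Background predicts. In addition, if the Feeding time item alone were followed, PN time would nearly coincide with time to full enteral nutrition, although the plan treats them as two endpoints.

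**Working it through.** The plan states no figure for this point, so there is none to reproduce. The check sets the rules side by side and then converts the gap between them into days.

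**Step 1. The rules by enteral intake, kcal/(kg/d)**

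| Intake | Feeding time item | Calorie control item |
|---|---|---|
| below 80 | PN given | PN given |
| 80 to below 100 | PN given | PN may already be stopped |
| 100 | PN may end, if full enteral nutrition is read at 100 | PN stopped |
| above 100, below 120 | PN still given if full enteral nutrition is read at a higher value | PN stopped |
| 120 and above | PN ended | PN stopped |

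The gap between the rules is therefore:
- 0 if both are read at 100;
- 20 at matching ends or midpoints (80 v 100, 90 v 110, 100 v 120);
- 40 at the widest (80 v 120).

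**Step 2. Inputs**
- Energy density (Table 1): preterm formula 80 kcal/100 ml = 0.80 kcal/ml; EHF 66 kcal/100 ml = 0.66 kcal/ml.
- Daily milk increase (Table 2): 12 ml/kg/d below 1000 g, 12–24 for 1000–1500 g, 24–36 for 1501–2000 g, 36 above 2000 g.
- Usual ceiling for total fluid (Fluid amount control): 180 ml/(kg/d).
- Assumption: milk advances without interruption.

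**Step 3. Milk volume at each threshold = threshold ÷ energy density**
- Preterm formula: 80/0.80 = 100, 100/0.80 = 125, 120/0.80 = 150 ml/kg/d.
- EHF: 80/0.66 = 121.2, 100/0.66 = 151.5, 120/0.66 = 181.8 ml/kg/d.

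**Step 4. Days between rules = volume gap ÷ daily increase**

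A 20 kcal gap is 25 ml/kg/d of preterm formula (20/0.80) or 30.3 of EHF (20/0.66). A 40 kcal gap is 50 or 60.6.

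| Increase (ml/kg/d) | 20 kcal, preterm | 20 kcal, EHF | 40 kcal, preterm | 40 kcal, EHF |
|---|---|---|---|---|
| 12 | 2.1 | 2.5 | 4.2 | 5.1 |
| 24 | 1.0 | 1.3 | 2.1 | 2.5 |
| 36 | 0.7 | 0.8 | 1.4 | 1.7 |

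For the same kcal gap, the EHF shift is 0.80/0.66 = 1.21 times the preterm one.

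**Step 5. Feasibility of the upper end**

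On EHF, 120 kcal/(kg/d) needs 181.8 ml/kg/d of milk alone, just over the usual 180. At 180 ml/kg/d EHF supplies 180 × 0.66 = 118.8 kcal/(kg/d). The 5.1-day figure is therefore an outer limit.

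**The case against.** The strongest reply is that only one stop rule is written. The Calorie control sentence is not self-contradictory: it can be read as two successive milestones, PN off first and full enteral nutrition later. The Feeding time item would then be general background, separating partial PN while feeds are incomplete from complete PN during fasting. The separate listing of the two endpoints fits that reading. This has force, but the article does not say which item governs, and the literal texts differ. Even if Calorie control alone governs, its trigger runs from 80 to 100, which is the 20 kcal gap already sized. Condensation into an article may explain missing detail, but not two printed statements that disagree.

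A second reply is that time to full enteral nutrition is already an endpoint, so a derived intake time adds little. That is partly fair, but the criterion for that endpoint is itself a range (100–120), so a fixed value is still needed.

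A reader might infer three stronger points that the documents do not support.

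- **A conflict with the fluid target.** Milk of 100 or 121 ml/kg/d when PN stops at 80 kcal/(kg/d) lies below the target in "to reach 150 ml/(kg/d) by the end of the first week". But that target covers all fluids, including other intravenous and oral medication, and may be adjusted daily. Milk below 150 is not by itself a breach.
- **The rule decides who has PN-associated cholestasis.** In infants below 1000 g fed from day 2 without interruption, the choice of rule moves the end of PN from day 10 to day 12–14 on preterm formula, and from day 12 to day 14–17 on EHF. This only borders the 14-day criterion, and day 17 implies 16 × 12 = 192 ml/kg/d, above the usual ceiling. The diagnosis also needs raised direct bilirubin, clinical signs and exclusion of other causes.
- **The comparison is biased.** Staff know the formula and the expected direction, so bias can enter, but nothing shows that they would apply the rules differently by arm.

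**Conclusion.** The point stands as an inconsistency that affects a listed secondary endpoint. The two items agree only at 100 kcal/(kg/d), and neither fixes a trigger. PN time per infant can shift by 0 days (both read at 100), by about 0.7–2.5 days (20 kcal gap), or by up to about 4 days on preterm formula and 5 on EHF (80 v 120). The day counts rest on Table 1 densities, Table 2 increments and uninterrupted advancement. The plan itself expects intolerance in 75–85 % of infants, so many will be interrupted, and an interruption falling between two thresholds lengthens the gap. The larger values apply to the slowest increments; at 24–36 ml/kg/d a 20 kcal gap is 0.7–1.3 days. The primary endpoint does not depend on when PN is stopped. No judgement is made here on which threshold is clinically right.

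**What to change.** 1. **Protocol text.** Reconcile the Feeding time and Calorie control items into one PN-stop rule, applied identically in both arms. The sponsor and clinicians choose the value.
2. **Supportive analysis.** Before any comparison by arm, fix one enteral-intake value. From the daily milk volumes and calories already recorded (Collection of clinical data during the NICU stay), derive the first day on which it is reached. Report that time beside actual PN time, so that the conclusion does not rest only on when staff removed PN.
3. **State the energy-density effect.** At equal milk volume, a kcal-based value takes longer to reach on EHF. For illustration, 80 kcal/(kg/d) needs 121.2 − 100 = 21.2 ml/kg/d more, or 21.2/12 = 1.8 days at the slowest increment, with no difference in tolerance. Report a volume-based version (ml/kg/d) as well, and interpret the two together.

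The cost is a wording change, one or two derived variables and some loss of bedside discretion. No extra infants, visits or measurements are needed.
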